## Abstract

**Introduction:**

Generalized anxiety disorder (GAD) is a common mental disorder that often begins in adolescence or early adulthood and is characterized by widespread and persistent anxiety. Partial sleep deprivation (PSD) is an important risk factor for GAD development and a common comorbidity. Adolescence is a period of rapid brain and nervous system development, and during this time, the occurrence of GAD can lead to neurocognitive deficits, such as impaired attention, cognitive control, and attention bias, that significantly affect cognitive function. However, relatively little research has been conducted on GAD comorbid with PSD in early adulthood compared with other psychiatric disorders. Clinical studies have demonstrated the effectiveness of acupuncture in treating GAD and sleep disorders, but the mechanism of how acupuncture modulates neurocognitive processing in patients with GAD comorbid with PSD has not been clarified.

**Methods/design:**

In this randomized clinical trial, a total of 56 participants diagnosed with GAD comorbid with naturally occurring PSD and 28 healthy controls (HCs) will be recruited. The participants diagnosed with GAD comorbid with PSD will be randomly assigned to either the acupuncture group or the sham acupuncture group at a 1:1 ratio. The primary outcome measure is the Hamilton Anxiety Rating Scale (HAMA). Secondary outcome measures are the Sleep Deprivation Index (SDI), the Self-Assessment Scale for Anxiety (SAS), the Epworth Sleepiness Scale (ESS), and the State-Trait Anxiety Inventory (STAI). Additionally, three psychological paradigms (the attentional network test, psychomotor vigilance test, and emotional face Go/No-go) and event-related potential (ERP) data. Healthy volunteers will not undergo acupuncture but will instead participate in baseline assessments for the scales, mental paradigms, and ERP data. Acupuncture and sham acupuncture interventions will be conducted for 30 min, three times a week, over a 2-week period. Evaluations will be performed at zero weeks (baseline), 1 week, and 2 weeks, with the data enumerator, outcome assessor, and participant blinded to the treatment assignment.

**Discussion:**

This study contributes to the exploration of the effects of acupuncture on improving anxiety symptoms and cognitive functions in individuals with comorbid GAD and PSD.

**Trial registration:**

ClinicalTrials.gov, ChiCTR2400082221. Registered March 25, 2024.

## 1 Introduction

### 1.1 Partial sleep deprivation leads to anxiety disorders in early adulthood

The National Sleep Foundation defines partial sleep deprivation (PSD) in early adulthood as sleeping < 6 h (1). Sleep and mood are closely related, and studies have shown that sleep deprivation is associated with increased physiological arousal, decreased ability to experience positive emotions, and increased sensitivity to negative emotional experiences (2). Sleep disorders are a major predictor of anxiety attacks (3), and they are also responsible for the onset of anxiety symptoms and the worsening of baseline anxiety states. A study of sleep conditions and anxiety states showed that naturally occurring partial sleep deprivation in school students led to increased levels of self-reported anxious arousal symptoms the next day (4). Naturalistic studies of the relationship between sleep and mood experiences in non-clinical samples have also shown that shorter sleep duration is typically associated with increased negative mood and anxiety and depressive symptoms the next day (5).

Generalized anxiety disorder (GAD) is characterized by widespread and persistent anxiety, accompanied by palpitations, sweating, tremors, dry mouth, sleep disturbances, irritability, poor concentration, and muscle tension, often starting in adolescence or early adulthood. GAD is often comorbid with other types of anxiety disorders and mood disorders, with sleep disorders or insomnia being one of the most predominant comorbidities (6). Sleep disorders are very common in individuals experiencing anxiety and are a defining criterion for many anxiety or anxiety-related disorders (7). Individuals suffering from anxiety often exhibit sleep disturbances, particularly sleep deprivation (8), that can trigger or further exacerbate anxiety symptoms (9). Psychobiological models suggest that a state of hyperarousal is a key factor in insomnia (10–12). Insomnia may be due to excessive cognitive dysfunction, maladaptive behaviors, physiological hyperarousal, and mental hyperarousal. Individuals suffering from insomnia often worry about sleep deprivation and the consequences of sleep deprivation; therefore, their anxiety-related beliefs, attitudes, and behaviors contribute to the persistence or worsening of sleep disturbances and severely shorten sleep duration (13). In summary, sleep deprivation is an important risk factor for generalized anxiety disorder and its common comorbidity, and there is an interactive relationship between the two.

### 1.2 Comorbidity of GAD and PSD is associated with cognitive dysfunction

It has been found that patients with anxiety disorders often have unconscious emotional processing deficits, working memory deficits, and attention and vigilance deficits. In addition, negative cognitive processing bias is one of the most important causes of the emergence, persistence, and development of anxiety (5). GAD in early adulthood is often accompanied by varying degrees of neurocognitive dysfunction that affects the ability to learn and remember, make behavioral decisions, and perceive and comprehend feelings. These lead to impairments in executive functioning, attention, memory, and information processing speed (14). These may manifest as procrastination, lack of confidence, indecisiveness, poor decision-making, distractibility, and memory loss, but the specific manifestations vary from person to person (15). Adolescence is a time of rapid brain development, and naturally occurring PSD during adolescence or early adulthood can lead to cognitive declines in learning and memory (16). Some studies have concluded (17) that insomnia in adolescents can affect their cognitive deficits directly or indirectly through the chain-mediated effects of fatigue, depression, and anxiety. In a study of college students, participants in the sleep deprivation group were deprived of sleep for 24 h, whereas participants in the non-sleep deprivation group were allowed to sleep in their beds for ~8 h under normal sleep conditions. Afterward, all participants completed cognitive tasks. Participants also provided self-assessment reports on their mood, effort, attention, performance estimates, and off-task cognition (18). Results indicated that participants in the sleep deprivation group performed significantly worse on the cognitive tasks compared with the non-sleep deprivation group. However, participants in the sleep deprivation group rated their attention, effort, and performance estimates higher than participants in the non-sleep deprivation group. This study suggests that college students may not be fully aware of the negative effects of sleep deprivation on their cognitive abilities. Investigating the neurobiological mechanisms underlying the comorbidity of GAD and early adult sleep disorders may help improve cognitive functioning in patients with GAD and may have important implications for the diagnosis, prevention, and treatment of GAD and related psychiatric disorders.

### 1.3 Acupuncture has favorable clinical efficacy in treating GAD and sleep disorders

Currently, the treatment of GAD involves medication and psychotherapy. Psychotherapy, while effective, typically lasts longer, requires a long-term commitment, and may not produce sustained symptom relief (19). If symptoms do not improve or only partially improve after a certain period of treatment, medication may be required. Medication primarily involves the use of benzodiazepines, 5-HT1A receptor partial agonists, and antidepressants with anxiolytic effects, such as SSRIs and SNRIs. Medication has been associated with a variety of side effects, including, but not limited to, addiction, medication tolerance, decreased attention to novel stimuli, memory loss, dizziness, nausea, diarrhea, decompensation, and weight gain (20). Currently, improvement rates with first-line treatment medications are typically 60%−70%. However, residual symptoms remain in 30%−60% of cases (21).

Acupuncture is an effective, safe, intervention with low side effects. Clinical studies have shown that acupuncture can significantly improve sleep quality and cognitive function in individuals with sleep deprivation (22) and rapidly reduce anxiety levels in patients with anxiety (23). Brain function research confirms that patients with anxiety and sleep disorders exhibit deficiencies in the default mode network. Repetitive negative thinking caused by poor sleep quality inhibits default mode network activation and internal functional connectivity, thereby reducing the ability to inhibit and regulate anxiety symptoms (24). There is a high degree of overlap between brain regions responsive to acupuncture and those within the default mode network (25). Research indicates that acupuncture can modulate functional connectivity within the default mode network (26–30), and increasing the number of acupuncture points or the intensity of stimulation can enhance regulation of the default mode network (31). However, the clinical efficacy and influence on cognitive processing pattern of acupuncture in patients with GAD comorbid with PSD remain unclear. Given this, the present study uses the General Anxiety Disorder-7 (GAD-7), the Self-Rating Anxiety Scale (SAS), the Hamilton Anxiety Rating Scale (HAMA), the State-Trait Anxiety Inventory (STAI) anxiety scales, the Sleep Deprivation Index (SDI), and the Epworth Sleepiness Scale (ESS) sleep scales to observe the clinical efficacy of acupuncture on patients with GAD comorbid with PSD. In addition, the event-related potentials (ERPs) in combination with the Go/No-go task, the attentional network test (ANT), and the psychomotor vigilance test (PVT) are used to observe the neurocognitive characteristics of PSD patients and the electrophysiological mechanism of acupuncture that affects the comorbidities of GAD and naturally occurring PSD to provide experimental evidence for the prevention and treatment of PSD in early adulthood.

### 1.4 Objectives

This study aims to observe participants with comorbid GAD and PSD to explore the intrinsic brain cognitive mechanisms associated with naturally occurring PSD in conjunction with GAD. Furthermore, the study seeks to investigate the clinical effects of acupuncture on improving both sleep deprivation and GAD symptoms in this comorbid population.

## 2 Methods/design

### 2.1 Study setting

This study will be a parallel randomized controlled clinical trial with the participants blinded to their groups. The research will be conducted in accordance with the principles outlined in the Consolidated Standards of Reporting Trials (CONSORT) and the Standards for Reporting Interventions in Clinical Trials of Acupuncture (STRICTA). A total of 56 participants diagnosed with GAD comorbid with naturally occurring PSD (i.e., nighttime sleep duration ≤ 6 h) will be recruited, and 28 healthy volunteers will also be recruited as a control group. Participants will be randomly assigned at a 1:1 ratio to either the acupuncture group or the sham acupuncture group. The establishment of the sham acupuncture group is intended to provide clearer evidence of the therapeutic effects of acupuncture and to compare these effects with the placebo effect of sham acupuncture. Both the acupuncture and sham acupuncture interventions will be conducted over a 2-week period, with sessions conducted three times a week. The study will be conducted at the Third Affiliated Hospital of Henan University of Chinese Medicine in Henan Province, China. The research will follow the Standard Protocol Items: Recommendations for Interventional Trials (SPIRIT) guidelines (32). For the participant timeline, see Figure 1.

**Figure 1 F1:**
[figure not shown]
SPIRIT table of the schedule of enrollment, interventions, and assessments. PVT, Psychomotor Vigilance Test; ANT, Attention Network Test; ERPs, event-related potentials; HAMA, Hamilton Anxiety Rating Scale; GAD-7, General Anxiety Disorder-7; SAS, Self-Rating Anxiety Scale; SDI, Sleep Deprivation Index; STAI, State-Trait Anxiety Inventory; ESS, Epworth Sleepiness Scale; and GO/No-go, Go/No-go Emotional Detection Paradigm.

### 2.2 Recruitment

The study will enlist participants with GAD and comorbid naturally occurring PSD (nightly sleep duration ≤ 6 h) from Longzihu University City and the East Minglu Campus of Henan University of Chinese Medicine through poster placement and online recruitment. Participants who meet the inclusion criteria, do not meet any exclusion criteria, and agree to participate in this trial will be included, and they will sign an informed consent form.

### 2.3 Inclusion criteria

The inclusion criteria are as follows:

1) Between 18 and 25 years of age.2) An average sleep duration equal to or < 6 h per night in the past 30 days.3) A score of ≥5 points on the 7-item Generalized Anxiety Disorder Scale (GAD-7).4) No anti-anxiety or insomnia-related medications taken or acupuncture treatments for anxiety or insomnia received in the most recent 30 days.5) Willingness to participate in the clinical study and sign an informed consent form.

### 2.4 Exclusion criteria

Participants with any of the following conditions will be excluded:

1) Organic mental disorders, anxiety, or depression related to surgical history or psychoactive substances.2) Family history of other mental illnesses, such as dementia, schizophrenia, mania, or addiction.3) Cognitive impairments that make subjects unable to cooperate.4) Pregnancy, preparing for pregnancy, or breastfeeding.5) Skin lesions or skin diseases, severe diabetes, tumors, or severe cardiovascular, lung, liver, kidney, and hematopoietic system diseases.6) Patients with contraindications to electroencephalography, as well as those with encephalitis, cerebrovascular diseases, or intracranial space-occupying lesions that affect the interpretation of EEG results.

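### Exclusion 2 is worded on family history only, so no listed criterion excludes a participant's own primary psychotic disorder or mania

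*Protocol article*

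**What the plan says.** All references are to the protocol article.

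- Exclusion 2 (section 2.4): "Family history of other mental illnesses, such as dementia, schizophrenia, mania, or addiction". It does not mention the participant's own history and does not say which relatives count.
- Exclusion 1 (section 2.4): "Organic mental disorders, anxiety, or depression related to surgical history or psychoactive substances".
- Exclusion 3 (section 2.4): "Cognitive impairments that make subjects unable to cooperate".
- Exclusion 6 (section 2.4) begins: "Patients with contraindications to electroencephalography, as well as those with encephalitis, cerebrovascular diseases, or intracranial space-occupying lesions".
- Inclusion 3 (section 2.3) sets the anxiety threshold by questionnaire score: "A score of ≥5 points on the 7-item Generalized Anxiety Disorder Scale (GAD-7").
- Inclusion 4 (section 2.3) is the only rule on drugs: "No anti-anxiety or insomnia-related medications taken or acupuncture treatments for anxiety or insomnia received in the most recent 30 days".
- Section 2.2 makes these lists decisive: "Participants who meet the inclusion criteria, do not meet any exclusion criteria, and agree to participate in this trial will be included".

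The remaining listed criteria concern age, sleep duration, consent, pregnancy or breastfeeding, and skin and systemic disease. The Discussion (section 3) describes screening of patients and healthy volunteers by the anxiety scale and the sleep index, and mentions no psychiatric history.

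**The concern.** An exclusion for serious mental illness would normally start with the person enrolled. This one names the illness in the family and leaves out the illness in the participant.

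That matters because of the trial's first aim. Section 1.4 seeks the brain cognitive mechanisms of partial sleep deprivation together with GAD, and section 3 says that the healthy group is there so that cognitive function and EEG can be compared with the patients. That comparison is not randomised, so the eligibility rules are its main protection. A psychotic or manic disorder that affects attention, inhibition or ERP components would be read as a feature of GAD with sleep deprivation. Mania is the most awkward case: it can itself shorten sleep, so it can help a person meet the sleep criterion for a reason other than the condition under study.

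**Working it through.** The article states no figure on this point, so there is none to reproduce. The check applies the listed criteria, as written, to four volunteers. Each is aged 18 to 25, consents, can cooperate, sleeps 6 h or less on average, scores at least 5 on the GAD-7, has had no anxiolytic, hypnotic or relevant acupuncture in 30 days, and has none of the conditions in exclusions 4 to 6.

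1. **Own primary schizophrenia or mania, no affected relative.** Exclusion 1 does not apply: the disorder is neither organic nor anxiety or depression tied to surgery or substances. Exclusion 2 does not apply: no relative is affected. Exclusion 3 does not apply: the person cooperates. Inclusion 4 does not bar other psychotropic drugs. Result: eligible.
2. **Own addiction, no affected relative.** Exclusion 1 applies if there is an organic mental disorder, or if the anxiety or depression is substance-related. Otherwise nothing applies. Result: partly covered.
3. **Own dementia.** This would count as an organic mental disorder under exclusion 1. Result: excluded, so there is no gap.
4. **No such illness, but a relative with schizophrenia who counts as family.** Exclusion 2 applies. Result: excluded.

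Volunteers 1 and 4 together show the inversion. It is complete for primary psychosis and mania, and partial for addiction.

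**Where the effect falls.** Let k be the number of such people among the 56 patients, and d the mean difference on some measure between them and the other patients. The article gives neither, so both stay as symbols.

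- Patients against 28 healthy controls: the patient mean moves by k × d / 56. With k = 1 this is d / 56 = 0.018 d. It acts in the direction of d and does not average out, because these people can enter only on the patient side if the controls are free of the disorder.
- Acupuncture against sham, planned at 28 per arm: with k_A and k_S such people in the two arms, the difference in means moves by (k_A − k_S) × d / 28. Under 1:1 randomisation the expected value of k_A − k_S is zero, so the expected shift is zero. With k = 1 the shift is +0.036 d or −0.036 d (1/28 = 0.036), with equal chance.

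The first comparison can therefore be biased. In the second, the cost is variance and chance imbalance.

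**The case against.** The strongest reply is that this is a slip in drafting or translation. The lead-in to section 2.4 speaks of participants who have the listed conditions, and the phrase on other mental illnesses follows directly from the participant's own disorders in exclusion 1. Personal or family history may well have been meant. That is plausible, but the published rule does not say it. If sites apply the intended rule, the text misdescribes who was enrolled; if they apply the text, the gap is real. Both cases call for a correction.

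A second reply is context. The abstract and section 2.1 describe participants diagnosed with GAD, recruitment is on university campuses, and section 3 calls the sample nonclinical. The full protocol may contain a diagnostic step that an article leaves out. Active psychosis or mania in students who attend six sessions and complete the ERP tasks would be uncommon. This limits the likely number of cases. It does not close the gap, because a disorder found at interview would still meet no listed exclusion.

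Third, excluding familial risk from a neurocognitive ERP study is a defensible choice, and the degree of kinship may be set in the full protocol. Both points stand. The concern is not that family history is used, but that personal history is absent.

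**Conclusion.** The point holds for the wording of exclusion 2 and should be corrected. As listed, the criteria admit a person with a primary psychotic disorder or mania and refuse a person who has only an affected relative. The main consequence is possible confounding of the patient-versus-healthy ERP and cognitive comparison. The size cannot be given: it depends on how many such people volunteer and how far they differ, and the article reports neither. The conclusion rests on the lists in sections 2.3 and 2.4 being applied as written.

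A reader might infer more than the documents support:

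- *That own addiction and own dementia are also wholly uncovered.* Exclusion 1 catches the first in part and would catch the second.
- *That the article itself calls these illnesses common in GAD.* Section 1.1 says "GAD is often comorbid with other types of anxiety disorders and mood disorders", which names neither psychosis nor addiction and does not specify mania.
- *That the family rule turns away a large share of volunteers, for example through a grandparent's dementia.* The article gives no frequency of affected relatives and does not say that grandparents count.
- *That the randomised HAMA result is biased.* Allocation balances such cases in expectation.
- *That assignment to sham endangers such participants.* The listed criteria do not bar other psychotropic drugs, so assignment to sham does not in itself remove treatment.

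**What to change.** Reword exclusion 2 so that it covers a current or past personal history of the listed disorders as well as a family history, and state which relatives count. Whether dementia stays among the family conditions is the investigators' choice and does not affect this point. Apply the same rule to the healthy controls, whose criteria the article does not list, so that both sides of the comparison are selected alike. If enrolment has begun, record for those already included whether a personal history was asked about and what was found.

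The cost is a one-line change to eligibility, one extra screening question and the loss of a few volunteers with a personal history. The sample size and the analysis are unaffected.

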### 2.5 Dropout criteria

Included subjects will be dropped from the study in the following cases:

1) Subjects with poor compliance who quit on their own during the treatment.2) Those who use treatment methods prohibited by this plan or change the treatment method on their own.3) Cases where serious adverse reactions or complications occur and are not suitable for continued treatment and the trial is terminated.

Dropped cases will be handled as follows:

1) After the subject drops out, the attending doctor will try to contact the subject to ask for the reason by visiting them after making an appointment by phone or letter, and they will then record the last treatment time and complete the assessable items.2) For cases that quit the trial due to adverse reactions or ineffective treatment, the attending doctor will take appropriate measures according to the actual situation of the subjects.3) The “Summary of Treatment Completion” and “Clinical Trial Completion” in the CRF will be filled in.4) All excluded and dropped cases will be subjected to intention-to-treat analysis after the trial ends.

### 2.6 Randomization

Using a simple randomization method, we will input the estimated sample size into the SPSS 18.0 statistical software package, generate random seeds, generate random numbers, obtain the permutation order to get the grouping results, make random cards, and then place them into opaque envelopes and seal them. During clinical implementation, the order of qualified cases included in the trial corresponds to the order of the numbers on the envelopes. We will open the envelopes in this order and group subjects according to the prompts on the randomized cards.

